##### Treatment allocation

Patients will be randomised to one of two parallel treatment arms allocated in a 1:1 ratio. Sealed numbered envelopes containing electronically randomised group allocations and group specific post-operative activity instructions will be prepared prior to trial commencement. Following informed consent, a sealed pre-randomised envelope will be allocated by the study nurse to the patient and the patient label affixed to the envelope. The envelope will then be handed to the treating physiotherapist to be opened postoperatively. The study interventions are specifically detailed on this instruction sheet and will be read by the physiotherapist to the patient postoperatively. For both allocation groups, the study card instructions are discussed and reinforced by the treating physiotherapist. The physiotherapist also gives the patient the activity monitor and instructs them on how to use this. The patient will receive a copy of the instruction card to take home and is advised not to disclose their allocation group to medical staff or assessors. The physiotherapist is not involved in subsequent assessment of the patient.

Post-operatively both groups will be fitted with electronic monitoring devices, worn on either the thigh under clothing or carried in the pocket, that will record patient position (sitting/lying/standing) and activity (walking/running/cycling). The devices will be taken off when showering or bathing.

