#### Control Treatment

Post-operative activity restrictions represent the traditional standard of care following lumbar microdiscectomy. As such the control group will be advised to follow post-operative activity restrictions for a period of one month following lumbar microdiscectomy. The control group will receive the following specific advice:

For the first one month following surgery:Avoid sitting for longer than 15–30 min in any two hour periodNo bending, lifting, twisting, pulling or pushing greater than 5 kgAvoid heavy domestic work such as vacuuming, laundry and making beds

And for the first two weeks following surgery:4.Avoid strenuous sexual activity

The restrictions detailed above reflect post-operative algorithms in current clinical practice. [unpublished data, [name] et al.].

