#### Statistical analysis

Hazard of reherniation and of parenteral analgesia will be compared by treatment arms. Efficacy will be defined as 1 minus hazard ratio of active vs restricted arms. Efficacy less than absolute delta (see sample size) will be deemed equivalent. Change from baseline adjusted for baseline in functional scores will be compared across treatment arms. Magnitude difference will be compared using ranksum (Mann-Whitney-U) test.

Analysis will report both intention to treat and per protocol results. Per protocol adherence to treatment will compare time in movement by treatment arm using t-test allowing for differential variance**.** Time in movement should differ between arms. Two thresholds will be defined a priori – a sedentary level below which will be considered adherent to movement restriction, and an activity level above which non-restriction will be deemed to have occurred. These thresholds will be used to define adherence. In sensitivity analysis we will examine impact on trial outcomes of excluding those subjects allocated to restriction who moved above this threshold and those unrestricted who were sedentary. We will also conduct sensitivity analysis by cross allocating such subjects.

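### Adherence is scored on time in movement, but the restricted arm is told to limit sitting, so a restricted patient who sits all day counts as adherent

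*Protocol article*

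**What the plan says.** Under Control Treatment, restricted patients are told for one month to avoid "sitting for longer than 15–30 min in any two hour" period. They are also told to limit bending, lifting, twisting, pulling and pushing (with a 5 kg figure) and to avoid heavy housework. For the first two weeks strenuous sexual activity is also to be avoided. Walking, standing and overall movement are not limited. Under Investigational treatment, the other arm may sit, exercise and work freely once they feel ready.

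The Background presents the wearable device as a way to observe whether sitting restrictions are followed. Treatment allocation and Activity monitoring/adherence both say that it records sitting separately from lying, standing, walking, running and cycling.

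Statistical analysis then sets the adherence rule:

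- The comparison: "Per protocol adherence to treatment will compare time in movement by treatment arm using t-test allowing for differential variance".
- The lower threshold: "a sedentary level below which will be considered adherent to movement restriction".
- The upper threshold: "an activity level above which non-restriction will be deemed to have occurred".
- Their role: "These thresholds will be used to define adherence".
- Their use: a sensitivity analysis "excluding those subjects allocated to restriction who moved above this threshold and those unrestricted who were sedentary", and a second one that moves the same patients to the other arm.

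**The concern.** The rule and the instruction concern different behaviours, and for the first item on the card they point in opposite directions. The card asks for less sitting. The rule rewards less movement, and sitting is one of the main ways to move less.

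What depends on this is the evidence on adherence. The Background presents device-tracked adherence, and its effect on outcome, as what is new in this trial. The Non-Adherence section expects that adherence may be poor in the restricted arm and gives that as a reason why measuring it matters. Question and Objectives ask whether unrestricted patients do worse, and Statistical analysis includes a rule for declaring the arms equivalent. For questions of that kind, non-adherence tends to make the arms look alike. A reader will therefore look to the adherence and per-protocol results to judge whether a null finding means anything. If the adherence label can be reversed, those results cannot serve that purpose.

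**Working it through.** The plan gives no figure to reproduce, so the check sets the instruction beside the rule. The only arithmetic is the sitting limit as a share of time.

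**Inputs.** Sitting limit: 15 to 30 minutes in any two hours (Control Treatment). Adherence rule: time in movement below a sedentary level (Statistical analysis). Device outputs: posture, including sitting, and type of activity (Treatment allocation; Activity monitoring/adherence). Waking hours per day are not given; 16 is assumed for illustration.

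**The limit as a share of time.** 15/120 = 12.5% and 30/120 = 25%. Over 16 waking hours this is 16 × 0.125 = 2 h to 16 × 0.25 = 4 h of sitting a day. With 14 waking hours it is 1.75 to 3.5 h, and with 18 it is 2.25 to 4.5 h.

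**Three patients under the rule.**

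| Patient | Relation to the instruction | Label from time in movement |
|---|---|---|
| Restricted, sits all waking hours | Exceeds the sitting limit by 1/0.25 = 4 to 1/0.125 = 8 times, whatever the waking hours | Almost no movement, so below any sensible sedentary level: adherent |
| Restricted, keeps to the sitting limit by walking | Follows the sitting item; walking is not limited | Movement time rises. If it passes the upper threshold: non-adherent, excluded or cross-allocated |
| Unrestricted, sits freely | Does what the advice permits | If movement time is low enough to be called sedentary: excluded, or moved to the restricted arm |

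The first row follows from the direction of the rule alone. The second and third depend on where the cut-offs fall. When the third patient is cross-allocated, someone whose behaviour the restricted arm was told to avoid is analysed as restricted.

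**Can a choice of cut-off repair this?** No. Two restricted patients can have the same low movement time, one standing or lying and the other sitting. Only the sitting record separates them, and the rule does not use it.

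**Does movement stand in for the other items?** Only crudely. Bending, lifting, load and housework are not among the outputs listed for the device, and minutes of walking do not measure load.

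**The case against.** The strongest reply has four parts.

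First, the main analysis is by intention to treat. The composite primary endpoint and the sample size do not use adherence, and exclusion and cross-allocation are labelled as sensitivity analyses. This stands. A reader might infer that the randomised comparison is compromised, and it is not.

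Second, the thresholds have no values here, a middle band between them is possible, and operational detail belongs in an analysis plan that is not shown. This stands for the walker and for the unrestricted sitter. It would be too strong to say that a restricted patient who walks instead of sitting will be scored non-adherent; the text supports only that this may happen. It does not rescue the all-day sitter, because the article already fixes the metric and its direction. The absence of numeric cut-offs is not part of the point.

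Third, several items on the card concern active behaviour, for which low movement is a rough proxy. This stands in part. It also means that sitting time covers one item only, so it would be wrong to present it as the single correct measure of adherence. A restricted patient who sits little but lifts and vacuums would pass on sitting time.

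Fourth, a reader might infer that time with the device off is counted as no movement and hence as adherence, since it is "worn on either the thigh under clothing or carried in the pocket" and is removed for bathing. The article does not say how such time is detected or scored, so that inference is unsupported and forms no part of the point.

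**Conclusion.** The point holds. The adherence rule in Statistical analysis does not measure the first restriction listed under Control Treatment, and it can reverse the label. A restricted patient who sits all day, at four to eight times the stated limit, is scored adherent under any sensible cut-off. Misclassification of restricted walkers and of unrestricted sitters is possible but depends on the cut-offs.

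The reach is limited to the between-arm adherence comparison, the per-protocol results, and the exclusion and cross-allocation analyses. How many patients would be mislabelled, and how far those results would shift, cannot be worked out from the article. The conclusion assumes only that time in movement excludes time spent sitting, which is the ordinary meaning of the words. The 16-hour day is illustrative, and the four- to eightfold figure does not depend on it. Because the question is one of inferiority or equivalence, the affected analyses carry real weight, and the rule should be corrected even though the intention-to-treat result does not need it.

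**What to change.** Reconcile the Background, Control Treatment and Statistical analysis sections before outcomes are examined, since redefining adherence afterwards would look data-driven.

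- Derive adherence to the sitting instruction from recorded sitting time, as the share of two-hour waking windows that stay within the protocol's own limit. Report it at both 15 and 30 minutes, without choosing between them.
- Compare sitting time between arms as the check that the arms separated.
- Do not score low movement alone as adherence to restriction. Revise the exclusion and cross-allocation rules to match, including the handling of unrestricted patients who sit freely.
- Keep time in movement as a supplementary measure.
- State that lifting, bending and housework are not among the device's listed outputs.

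No patient instruction changes and no new data are needed. The cost is analysis wording and some extra derivation from the device record. The remaining weakness is that adherence to the non-sitting items stays unmeasured by the device.

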## Methods

### Question

Is the outcome of patients without restrictions inferior to those observing sitting and activity restrictions following lumbar discectomy?

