#### Investigational treatment

The investigational treatment arm will be the group without sitting or other restrictions. They will be advised to return to normal activities with no restrictions placed on sitting, exercise, return to work, or other activities as soon as they feel ready.

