#### Non-Adherence

Patient data will be analysed on an intention to treat basis. Non-adherence to post-operative activity protocol may be determined by analysis of recorded activity from the wearable device. This will be especially important in light of the trial explaining to participants as part of consent procedures the clinical uncertainty regarding movement restriction, which may result in poor adherence in the group subsequently assigned to restriction.

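### The movement-based exclusion and cross-allocation do not match the advice given to either arm, and they are confounded by recovery, probably in favour of no restriction

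*Protocol article*

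**What the plan says.** All of this is in the protocol article.

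- **Non-Adherence:** "Patient data will be analysed on an intention to treat basis".
- **Statistical analysis:** "Analysis will report both intention to treat and per protocol results". Adherence is judged on time in movement, with two thresholds to be set in advance: "a sedentary level below which will be considered adherent to movement restriction, and an activity level above which non-restriction will be deemed to have occurred". The section expects movement time to differ between the arms.
- **Statistical analysis, sensitivity analyses:** the first examines the effect of "excluding those subjects allocated to restriction who moved above this threshold and those unrestricted who were sedentary". The second is as follows: "We will also conduct sensitivity analysis by cross allocating such subjects". The only adjustment named is for the baseline score in the functional outcomes.
- **Investigational treatment:** the unrestricted arm has "no restrictions placed on sitting, exercise, return to work, or other activities as soon as they feel ready".
- **Control Treatment:** the restricted arm is told to limit sitting, bending, lifting, twisting, pulling, pushing and heavy domestic work for a month, and strenuous sexual activity for two weeks. It sets no limit on walking or on total movement.
- **Question:** "Is the outcome of patients without restrictions inferior to those observing sitting and activity restrictions following lumbar discectomy"?

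**The concern.** There are two separate problems.

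First, the classifier does not measure adherence to what patients were told. An unrestricted patient who stays inactive because of pain is following advice to resume "or other activities as soon as they feel ready", yet is removed or switched as sedentary. A restricted patient who avoids sitting by standing and walking is following the control advice, yet can exceed the movement threshold and be removed or switched as active.

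Second, movement is recorded in the month after surgery, so it can reflect how well the patient is recovering. The rule takes the high movers out of one arm and the low movers out of the other. If movement and recovery are related, the arms that remain differ in prognosis, and cross-allocation adds to the imbalance.

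The trial asks whether no restriction is inferior. A bias towards no restriction is anti-conservative for that question and could hide a real disadvantage. These results will be read: the Background presents the effect of adherence on outcome as a novelty of the trial, and Non-Adherence expects poor adherence in the restricted arm.

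**Working it through.** **Step 1. Rule against advice (no arithmetic needed).**

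| Patient | Advice received | Status under the movement rule |
|---|---|---|
| Unrestricted, inactive because not yet ready | followed | sedentary: excluded, then switched |
| Restricted, keeps sitting short, walks a lot | followed on sitting | above the threshold: excluded, then switched |
| Restricted, sits for long periods, moves little | broken | below the sedentary level: counted as adherent |

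This mismatch holds whatever the threshold values are and needs no assumption about prognosis.

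**Step 2. Possible size of the bias.** The protocol gives no figure for these analyses, so there is none to reproduce.

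Inputs from the Sample size section: 80% success, and a difference of interest of 80% against 64%, which is 80 − 64 = 16 points. Inputs that are assumptions:
- no true effect of allocation or of movement on outcome;
- movement M and latent recovery U are normal with within-arm correlation r;
- the unrestricted arm moves d SD more;
- the two thresholds L and H are the tertiles of movement in both arms pooled.

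Success is U > −0.842 (the 20th percentile). L and H solve ½Φ(x) + ½Φ(x − d) = 1/3 and 2/3. The restricted arm keeps M ≤ H and the unrestricted arm keeps M ≥ L. By symmetry each arm keeps the same fraction k = Φ(H). Let s_U and s_R be the proportions of each randomised arm that are both kept and successful, from the bivariate normal distribution.

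- Exclusion: difference = (s_U − s_R) / k.
- Cross-allocation: difference = (s_U + 0.8 − s_R) − (s_R + 0.8 − s_U) = 2(s_U − s_R), which is 2k times the exclusion difference.

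Example with r = 0.3 and d = 0: L = −0.431, H = 0.431, k = 2/3. Success among those kept is 84.9% unrestricted and 75.7% restricted, a difference of +9.2 points. Cross-allocation gives 2 × (2/3) × 9.2 = +12.3 points.

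Unrestricted minus restricted, in percentage points, when the truth is 0:

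| r | Exclusion, d = 0 / 0.5 / 1.0 | Cross-allocation, d = 0 / 0.5 / 1.0 |
|---|---|---|
| −0.3 | −9.2 / −7.0 / −4.9 | −12.3 / −10.6 / −8.2 |
| 0 | 0 / 0 / 0 | 0 / 0 / 0 |
| 0.1 | +3.1 / +2.3 / +1.6 | +4.1 / +3.5 / +2.7 |
| 0.3 | +9.2 / +7.0 / +4.9 | +12.3 / +10.6 / +8.2 |
| 0.4 | +12.3 / +9.3 / +6.5 | +16.4 / +14.1 / +11.0 |

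The fraction of each arm affected is 33%, 24% and 16% at d = 0, 0.5 and 1.0. The intention-to-treat difference is 0 throughout, because no patient is removed or moved.

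**Step 3. Other thresholds.** A simulation at r = 0.3, with d from 0.25 to 1.0, used either one cut at the midpoint between the arm means or two cuts at the midpoint ± 0.5 SD. Exclusion gave +4.8 to +12.1 and cross-allocation +8.1 to +13.3. The order of size does not depend on the choice of tertiles.

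**Step 4. Excluding in the restricted arm only.** At r = 0.3, with the unrestricted arm left whole at 80%, the false advantage is 80 − 75.7 = 4.3, 80 − 76.8 = 3.2 and 80 − 77.9 = 2.1 points at d = 0, 0.5 and 1.0. It is smaller but not removed.

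**The case against.** A reader might infer that the rule necessarily creates a spurious benefit of no restriction. The documents do not support that. They give no relation between movement and recovery. The bias vanishes at r = 0 and reverses if the more active patients do worse, for instance if heavy activity led to reherniation. A positive r is plausible, because Primary endpoints says that reherniation and reoperation do not explain most unsatisfactory outcomes and the composite also rests on pain and disability. Plausible is as far as this goes.

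A reader might also take the artefact to equal the whole 16-point difference. In the tertile illustration that happens only for cross-allocation, at r = 0.4, with no separation in movement between the arms. The protocol expects the arms to differ in movement, and separation lowers the figures. With two thresholds, patients in between stay where they were randomised, so the contrast is not purely active against inactive patients.

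Nor do the documents show that the trial's main conclusion is compromised. Both analyses are labelled sensitivity analyses, intention to treat is the stated basis, and no passage makes per-protocol agreement a condition for any conclusion. There is no ground for saying that the bias serves a wished-for result: the Hypothesis section states that restriction improves outcomes.

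These points limit the size, direction and reach of the concern. They do not remove it. The mismatch with the advice needs no correlation, and the label of sensitivity analysis is only a partial defence, because the same thresholds define adherence and per-protocol results are reported beside intention to treat.

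**Conclusion.** The point stands in this form. The adherence rule misclassifies patients who followed their advice in either arm. The exclusion and cross-allocation analyses break randomisation by acting on opposite ends of a post-randomisation variable. They are open to confounding by recovery, probably towards no restriction, and so cannot support a conclusion that no restriction is not inferior.

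Under the stated assumptions the false difference is about +2 to +3 points by exclusion and +3 to +4 by cross-allocation at r = 0.1, +5 to +9 and +8 to +12 at r = 0.3, and +7 to +12 and +11 to +16 at r = 0.4. The correlation, the arm shift and the thresholds are all assumptions. The sign follows the sign of r. Intention to treat is unaffected, so this should be corrected but does not undermine the main analysis.

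**What to change.** 1. Define adherence by the advice given. In the restricted arm, use monitor-recorded sitting against the limit in the control advice; the device records posture. Do not count a sedentary unrestricted patient as non-adherent.
2. Drop the cross-allocation analysis. Replace it with a complier-average causal effect, with randomisation as the instrument and keeping to the sitting limit as the exposure, reported with its 95% CI. In its simplest form this is the intention-to-treat difference divided by the between-arm difference in the proportion keeping to the limit.
3. State the exclusion-restriction caveat. The advice also covers lifting, bending and domestic work, so allocation could affect outcome by routes other than sitting.
4. If a per-protocol set is kept, label it as confounded by recovery and do not use it to support a conclusion of no inferiority or equivalence. Limiting exclusions to the restricted arm reduces the bias but does not remove it, and adjusting for baseline covariates cannot remove confounding that arises from recovery after surgery.

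The cost is revised analysis wording and one extra model, with no new data. The complier estimate has a wider interval than intention to treat and rests on an added assumption that the data cannot fully test.

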## Discussion

The longstanding practice of applying post-operative activity restrictions following lumbar spine surgery was based upon the hypothesis that such restrictions may reduce the risk of progressive instability or lumbar disc reherniation [5]. Furthermore, prolonged sitting has been suggested to decrease lumbar lordosis, increase spinal loading and muscle activity and contribute to accelerated disc degeneration and low back pain independent of previous operative intervention [19]. The randomised controlled trial of Bono et al. [7] demonstrated no significant difference in outcome measures between patients who observed two weeks or six weeks of activity restrictions though was underpowered to detect differences in reherniation rates. The only prior studies investigating the impact of removing post-operative restrictions reported no increased risk of reherniation or reoperation in patients not observing activity restrictions following lumbar discectomy surgery but these studies lacked a comparator group and their design was subject to potential bias [5, 6]. Modern lumbar discectomy is now minimally invasive and results in less tissue destruction, further undermining the hypothetical rationale for activity restriction. In a recent survey of Australasian Neurosurgeons, many advised either no sitting restrictions (22%) or sitting as comfort allows (40%) [unpublished data, [name] et al.]. However, the vast majority (84%) advised restricted lifting.

In an uncontrolled prospective cohort study [6] patients who did not observe post-operative activity restrictions returned to work earlier. Mean time to return to work in the cohort was 1.2 weeks. Currently extant recommendations suggest four to 16 weeks off work following lumbar discectomy surgery.

